# Summary

This internal protocol outlines two online randomised control trials (RCT) to test the relative effects of added sugar labelling on Australians’ intended food and beverage purchases. It will be adapted for the Australia New Zealand Clinical Trials Registry and ethics applications. Australian adults aged 18 years and older will be recruited using a recruitment agency. Trial 1 (n=1,008) will determine the relative impact of 7 different added sugar labelling options on healthiness of intended purchases of breakfast cereals, yoghurts and non-alcoholic packaged beverages. Trial 2 (n=1,152) will examine: (i) the relative effect of different combinations of multi-labelled food and beverage products (informed by the two most effective labels in Trial 1); and (ii) effects by level of participant sugar consumption, gender, age, education, and income. This new evidence will guide and inform the development of effective labelling policies to reduce added sugar consumption for Australians and New Zealanders.

## Background:

“Added” sugars include sugar added to foods and beverages in the production or cooking process (1). “Free” sugars are a broader category of sugars, and include “all monosaccharides and disaccharides added to foods by the manufacturer, cook, or consumer, plus sugars naturally present in honey, syrups, and fruit juices and fruit juice concentrate” except those that are naturally occurring or present in foods such as fruits, vegetables and milk (2). For consistency, in this protocol we will refer to any sugar-based ingredient added to food as “added” sugar and this may include “free” sugar as well, as per the terminology used by the Food Regulation Standing Committee (FRSC) policy consultation paper on sugar labelling (3) which is the prompt for this study. Over half of Australians (52%) exceed the World Health Organization (WHO)’s recommended intake of added sugar (2), increasing their risk of obesity, Type 2 Diabetes, dental decay, and some cancers. Further, the majority (90%) of Australians also exceeded the WHO conditional recommendation that added sugars be reduced to less than 5% of energy intake, where additional healthy benefits have been shown (2). Added sugar intake, and the burden of related chronic diseases, are disproportionately higher for disadvantaged populations in Australia (4). While there is empirical evidence that increased nutrition knowledge increases dietary quality (5, 6), packaged food in Australia is not currently required to display added sugar content, either on front-of-package or in the nutrition information panel on the back or side of the pack. This is an area of strong public and policy interest internationally. There is moderate to strong evidence from laboratory trials that front-of-package added sugar warning labels reduce intended purchasing of sugar-sweetened beverages (7). This includes evidence from our previous online randomised control trial (RCT) which demonstrated that front-of-package labels, including graphic warning labels, reduced intention to purchase sugar-sweetened beverages among Australians aged 18-35 years (8). However, there is limited evidence of labelling effects on actual or intended food purchases for foods other than sugar-sweetened beverages. The Australian and New Zealand Government Food Regulation Standing Committee (FRSC) is exploring options for labelling of added sugars on packaged foods and drinks available for sale in Australia and New Zealand, to support consumers in making informed choices to reduce their added sugar intake. FRSC has identified a number of literature gaps hindering policy development, including evidence: (i) on labelling for products other than sugar-sweetened beverages, including seemingly “healthy” food products such as flavoured yoghurt and breakfast cereal; (ii) involving Australian and New Zealand consumers; and (iii) on the differential impact for different population subgroups (3). While FRSC is considering policies requiring display of multiple sugar labels simultaneously, we are not aware of evidence to date testing the effect of displaying multiple added sugar labels at once.

This new evidence will be critical to the development of effective labelling policies to reduce Australian and New Zealand added sugar consumption.

Research question:

#### Primary

What is the impact of added sugar labels on intended purchase of selected high sugar food and drink products?

#### Secondary

What is the impact of different combinations of added sugar labels on intended purchase of selected high sugar food and drink products?

How does the effect of added sugar labels on intended purchase of selected high sugar food and drink products differ according to participant characteristics (including age, gender, education, income, or usual levels of sugar consumption)?

Hypothesis:

#### Primary

Added sugar labelling on food and drink items reduces the proportion of intended purchases that are high sugar products, compared to no added sugar labels.

#### Secondary

Displaying multiple added sugar labels on food and drink items reduces the proportion of intended purchases that are high sugar products, compared no labels or display of one added sugar label.

Participant characteristics including age, gender, education, income, and usual levels of sugar consumption alter the effect added sugar labelling on intended purchasing.

## Methods:

### Overall approach:

The project will consist of two phased online RCTs. The results from Phase 1 (Trial 1), will inform the design of Phase 2 (Trial 2). Online RCTs are useful for testing policies that are not yet implemented in the real world, and are able to test relative effectiveness across a number of different scenarios.

#### Trial 1 methods:

We will examine the relative effectiveness of different labelling options for three food product groups (breakfast cereals, yoghurts and non-alcoholic packaged beverages). These food groups have been chosen as they make a significant contribution to Australians’ energy intake, and because there is a wide variation in added sugar content of available products. According to the Australian National Health Survey (AHS) 2011-12, overall 36% of Australians and 16% of Australians consumed ready to eat breakfast cereals and yogurt, respectively, in the 24 hours prior to the survey. Additionally, just over half (52%) of added sugars in the diet were consumed from beverages, with the leading beverages being soft drinks, electrolyte and energy drinks (19%), fruit and vegetable juices and drinks (13%), and cordial (4.9%) (4).

1,008 Australian adults aged ≥18 years reporting regular (once a month or more) purchase of yoghurt, breakfast cereals and non-alcoholic packaged beverages will be recruited through an online panel provider. Sample size calculations are detailed below. Eligible participants will be randomised to complete one of seven online survey conditions in Qualtrics. Each survey condition will include of three hypothetical purchasing tasks: one each for breakfast cereals, yoghurts and non-alcoholic packaged beverages. Each task will consist of selecting between ten different products with varying sugar content, labelled with one of seven labelling options (depending on the survey condition) currently used in Australia or internationally or under consideration by the Australian Government: (i) Status quo – current Nutrition Information Panel (NIP) (Back of Pack labelling system without added sugar content) (control condition); (ii) added sugars quantified in the NIP (the remaining five conditions will also include a back-of-pack NIP with added sugar content); (iii) Pictorial approaches to convey the amount or types of sugars in a serving of food (teaspoons of sugar); (iv) Chilean-style advisory labels for foods high in added sugars; (v) Health Star Rating (using current algorithm without added sugar)- simple display without panel; (vi) Health Star Rating (using proposed algorithm with added sugar)- simple display without panel; and (vii) Change to statement of ingredients to asterisk ingredients with added sugar. Advisory labels will be displayed on high sugar products only. All other labels will be displayed on every product in the choice set, as relevant. Each participant will be exposed to one treatment condition (sugar labelling intervention or control) and complete the purchasing task in all three food categories (Figure 1).

| Label 1: Status quo – current Nutrition Information Panel (NIP) (Back of Pack labelling system without added sugar content) (control condition)  Label 2: Added sugars quantified in the NIP  Label 3: Pictorial approaches to convey the amount or types of sugars in a serving of food  Label 4: Chilean-style advisory labels for foods high in added sugars; (v) Health Star Rating  Label 5 and 6: Health Star Rating  Label 7: Change to statement of ingredients to asterisk ingredients with added sugar | [figure not shown]  [figure not shown]  [figure not shown]  [figure not shown]  [figure not shown]  [figure not shown] |
| --- | --- |

Figure 1: Examples of intervention labels 1-7 used in the choice experiment study. Health Star Rating trademarks are owned by the Commonwealth of Australia. Further information on the Health Star Rating can be found at www.healthstarrating.gov.au

#### Calculating added sugar content

‘High sugar’ products will be classified using the UK Nutrient Profiling Model (foods >6.25g added sugar/100g and beverages >3.13g/100mL (9).

In order to determine added sugar in branded yoghurt and breakfast cereals we will make use of the AUSNUT database (10) and a standard protocol (11). To calculate added sugar we use the following decision tree: i) if the ingredients list includes added/free sugars only then the total sugars will be considered added sugars; ii) if the ingredients list includes a mixture of added sugars and intrinsic sugars then we will allocate added sugar as a percentage of total sugar content, based on the percentage added sugar content of a similar generic product in AUSNUT database. We will use AUSNUT “free sugars” content to calculate this.

For water-based beverages we will assume that all sugars are added sugars. For fruit juices, we will select branded drinks that provide the percentage of juice the product so we can calculate added sugar content.

To calculate the modified Health Star Rating including added sugar, we will use the UK scale for 10% added sugar intake (12).

#### Selection of food products for testing

Branded food products will be used to increase the realism of choice tasks for participants, in order to maximise external validity. The selection of the 10 food products for testing in each category will be based on:

- Popularity according to Canstar reports (when available)
- Brands available at both Coles and Woolworths supermarkets
- Include a variety of flavours and products sub-categories, for example cereal flakes, cereals with added fruit etc.
- Including products with a range of added sugar contents

#### Piloting

The survey wording and flow will be tested within the research team, and wider research group. Prior to the full Trial 1 recruitment, there will be a ‘soft-launch’ of 100 participants to allow detection and correction of any survey errors. The ‘soft-launch’ will also allow the assessment of whether an appropriate range of branded products have bene included. When a participant has selected to ‘purchase’ no product, they will be asked to specify if there was another product they would have purchased if it was available.

#### Defining high sugar purchasers vs low sugar purchasers

Participants will be asked to select all relevant products they purchase at least once a month for themselves or their household from a range of generic product subcategories in each of the product categories of interest (yoghurt and custards, breakfast cereal and non-alcoholic packaged drinks). For example, in the yoghurt categories this will include plain Greek or natural yoghurt, flavoured Greek or natural yoghurt, custard etc. These generic subcategories will be classified as “high” and “low” sugar products. If the participants selects one or more high sugar products in each category they will be considered a high sugar purchaser. We will implement a quota for half of all participants to be classified as “high sugar purchasers”.

#### Trial 2 methods:

The seven labelling options in Trial 1 are distinct and could feasibly be combined for potential increased effect. We will examine the effect of displaying multiple labels simultaneously and effects for different consumer subgroups. The two most effective labels from Trial 1 will be used to determine four test scenarios for Trial 2: Label A; Label B; Label A+B; Status quo (control condition). 1,152 Trial 2 participants will be recruited.

### Sample size calculations:

Sample sizes of 144 completed participant surveys per subgroup for Trials 1 and 2 are based on detection of 32% difference in intended purchasing of high versus low sugar products, with a statistical significance level of 5% and 80% power (based on Billich et al. 2018 findings, smallest difference detected between baseline purchases [64% purchased sugar sweetened beverages] compared to 28% to 47% participants across treatment groups, and approximately 10% unusable surveys due to errors)(8). Trial 1: 7 treatment groups x 144 participants per group= 1,008 participants. Trial 2: 4 treatment groups x 144 participants per group x 2 for subgroup analysis of high v. low sugar consumers= total 1152 participants.

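### The 32% detectable difference stated for 144 per group does not follow from the rates given beside it; those rates, and the sample size, correspond to 17 percentage points (64% v 47%)

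*Protocol*

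**What the plan says.** One paragraph of the Protocol, under sample size calculations, covers both trials. It sets 144 completed surveys per subgroup and says that these sizes "are based on detection of 32% difference in intended purchasing of high versus low sugar products". Significance is set at 5% and power at 80%. The bracket that follows gives the basis as an earlier online trial by the same group: "smallest difference detected between baseline purchases [64% purchased sugar sweetened beverages] compared to 28% to 47% participants across treatment groups". It also makes an allowance for "approximately 10% unusable surveys due to errors". The totals come from multiplication: "7 treatment groups x 144 participants per group= 1,008 participants" for Trial 1, and four groups of 144, doubled for high and low sugar consumers, giving 1,152 for Trial 2.

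The paragraph does not say whether 32% is absolute or relative, what it is relative to, whether the test is one- or two-sided, or whether 144 is the count before or after unusable surveys are removed.

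**The concern.** The sentence contradicts itself. It calls the design difference the smallest one seen in the earlier trial and gives it as 32%. From 64%, treatment rates of 28% to 47% give differences of 17 to 36 percentage points, so the smallest is 17, not 32. Relative to 64%, the smallest is 26.6%.

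The detectable difference is what a reader uses to interpret a null result. The primary outcome is a difference in proportions, so a bare percentage difference can easily be read as percentage points. On that reading the trials look able to find only very large label effects, when they were sized for an effect about half as big. Someone re-checking the calculation with 32 points would get about 40 per group and might conclude that the trial is some three and a half times larger than needed. The same figure supports both trials and the doubling in Trial 2. The Protocol's summary says the text will be adapted for the trial registry and the ethics application, so the figure could be carried into those records.

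**Working it through.** **Inputs, all from the sample size paragraph.** Baseline 64%; treatment groups 28% to 47%; significance 5%; power 80%; about 10% unusable; 144 per group. Two-sided testing is my assumption, since the text does not say. It gives z = 1.960 for significance and z = 0.842 for power.

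**Formulas, per group, 1:1.**
- Unpooled: n = (1.960 + 0.842)² × [p1(1-p1) + p2(1-p2)] / (p1-p2)², where the squared sum is 7.849.
- Pooled: n = [1.960 × √(2·p̄(1-p̄)) + 0.842 × √(p1(1-p1) + p2(1-p2))]² / (p1-p2)², where p̄ is the mean of the two rates.
- Loss of 10%: n/0.9, or the cruder n × 1.1.

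**Step 1: reproduce 144 from 64% v 47%.**
- Unpooled: 7.849 × (0.2304 + 0.2491) / 0.17² = 7.849 × 0.4795 / 0.0289 = 130.2.
- Pooled (p̄ = 0.555): 133.0.
- With loss: 130.2 × 1.1 = 143.2 and 130.2/0.9 = 144.7; 133.0 × 1.1 = 146.3 and 133.0/0.9 = 147.7.

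The stated 144 lies within this range of 143 to 148. One-sided versions of the same comparison need only 103 to 105 before loss and 115 to 117 after, or 117 and 130 with a continuity correction. The figure is therefore consistent with a two-sided test.

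**Step 2: try 32% in its usual senses.**

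| Reading of 32% | Rates | n before loss | n with 10% loss |
|---|---|---|---|
| Absolute, 32 points | 64% v 32% | 34.3 to 37.1 | 38 to 41 |
| Relative to 64% | 64% v 43.5% (0.64 × 0.68) | 89.1 to 91.8 | 98 to 102 |
| Rates given in the text | 64% v 47% | 130.2 to 133.0 | 143 to 148 |

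The absolute reading cannot be rescued by choosing other rates: the largest n for any pair 32 points apart is 38 per group before loss.

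**Step 3: what 144 can detect (pooled test, 64% at baseline).** Removing 10% leaves 144 × 0.9 = 129.6, about 130.

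| Analysed per group | Power, 17 points | Power, 32 points | Power, 32% relative | Smallest difference at 80% power |
|---|---|---|---|---|
| 144 | 83.1% | over 99.9% | 94.0% | 16.3 points |
| 130 | 79.1% | over 99.9% | 91.6% | 17.2 points |

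The stated 80% power goes with 17 points and about 130 usable surveys.

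**Step 4: look for a route to 32%.** From 64% and 47%: 17/64 = 26.6%; 17/47 = 36.2%; one minus the odds ratio = 50.1%; 17/53 = 32.1%. The last divides the difference by the 53% who did not choose a sugary drink under the label. It is the only route from these rates that I found.

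**Step 5: totals.** 7 × 144 = 1,008 and 4 × 144 × 2 = 1,152. Both are correct.

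**The case against.** The strongest reply is that nothing in the design depends on the number 32. The correct inputs stand beside it, a careful reader can derive 17 points from the same sentence, and the sample sizes are right. That stands, and it limits the point to a correction of one stated figure.

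A second reply is that 32% may be undefined rather than wrong, because 17/53 gives 32.1%. That is possible. But the Protocol does not state this base, it is not the usual one for a relative difference, and even if it was meant the design difference is still 17 points.

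A third reply is that 64% v 47% is not the only pair of rates that lands near 144. This is true: 50% v 34% (a 32% relative reduction) gives 146 unpooled without loss, or 129 one-sided with continuity correction and 144 after loss. The text gives no such rates, however, and it does give 64% and 47%. Similarly, 64% v 47% with continuity correction and no allowance for loss gives 145, so arithmetic alone does not settle whether 144 is before or after unusable surveys. Because the paragraph lists the 10% as part of its basis, the inflated reading is the more natural one.

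Three stronger inferences are tempting, and the document does not support them:
- **That the sample size is wrong, or the trial badly oversized or undersized.** The 144 agrees with the Protocol's own rates. If 32% is read as points, the trial is more sensitive than the text says, not less.
- **That the figure is wrong by almost a factor of two.** This holds only if 32% is absolute, which the text does not say. Against the 26.6% relative reduction, the ratio is 32/26.6 = 1.2.
- **That 80% power is overstated because Trial 1 sets six labels against one control.** The primary hypothesis is a general one, labelling against no labelling, and the primary outcome section names logistic regression across groups. Neither prescribes six unadjusted pairwise tests. Adjustment is commonly left to a statistical analysis plan, which is not at hand, so its absence here is not a fault.

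**Conclusion.** The point holds as a correction of a stated planning figure that should be made. The difference of 32% contradicts the rates in its own sentence. Those rates give 17 percentage points (26.6% relative), and 17 points is also what 144 per group corresponds to: 143 to 148 by calculation, against 38 to 41 for 32 points and 98 to 102 for a 32% relative reduction. Either the figure is wrong or its base is unstated and unconventional.

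The conclusion assumes a two-sided 5% test of two independent proportions with equal groups. The power figures check the calculation as the Protocol presents it, with one binary outcome per participant. Each participant completes three purchasing tasks, so these figures should not be taken as the power of the final analysis.

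**What to change.** In the sample size paragraph, replace the 32% difference with 17 percentage points (64% v 47%). If 32% is to be kept, define its base and give the 17 points beside it.

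In the same sentence, state three things:
- that the 5% level is two-sided;
- that 80% power refers to a single label-control comparison;
- whether 144 is counted before or after removal of the approximately 10% unusable surveys. The arithmetic suggests before, leaving about 130 usable per group, but the authors need to confirm this.

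The cost is one corrected sentence, repeated wherever the figure has been copied into the registry entry or the ethics application. The sample sizes of 144, 1,008 and 1,152, the design and the recruitment do not change.

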### Recruitment:

A third-party recruitment company will be used to recruit participants for the online study. The recruitment company have security measures in place to securely store participants’ identifiable data. No identifiable information will be received by the researchers from the recruitment company. Research data (i.e. answers to the survey) will not be available to or stored by the recruitment company.

#### Eligibility

- Australian residents over the age of 18 years
- Access to a computer and internet connection
- Regular (at least once a month or more) purchasers of breakfast cereal, yoghurt and non- alcoholic pre-packaged drinks for themselves or their household
- Completes at least one supermarket shop per month for their household
- Lives with at least one child <18 years at home

### Analysis for Trials 1 and 2:

#### Primary outcome:

The differences in the proportion of high sugar products among intended purchases across treatment groups which will be examined using logistic regression analyses. “High” sugar products will be classified using the UK Nutrient Profiling Model (foods >6.25g added sugar/100g and beverages >3.13g/100ml)(9).

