#### Secondary outcomes:

The differences between treatment groups in overall intended purchases by (i) added sugar content (g/100g); (ii) Health Star Rating (from 0.5 to 5); and (iii) percentage of Five Food Group (healthy) and discretionary (unhealthy) foods according to Australian Dietary Guidelines (13), which will be analysed using logistic or linear regression, as appropriate. Trial 2 results will be examined for the whole sample. We will then test for interaction with possible effect modifiers, including gender, age, education, and usual sugar consumption, and stratify analyses when an interaction term is significant at a p-value of <0.01. All analyses will be adjusted for key covariates.

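### The primary analysis does not say how up to three choices by one participant are handled; if they are pooled in ordinary logistic regression, type I error exceeds 5% whenever those choices are positively correlated

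*Protocol*

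**What the plan says.** Under Trial 1 methods, the participant is the unit of randomisation. "Each survey condition will include of three hypothetical purchasing tasks", one per product category, and "Each participant will be exposed to one treatment condition (sugar labelling intervention or control) and complete the purchasing task in all three food categories". The label is therefore constant within a person, who contributes up to three outcomes. The Piloting section shows that a participant may also choose no product.

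Under Primary outcome, in the analysis section that covers both trials, the plan takes the difference in the share of intended purchases that are high in sugar "across treatment groups which will be examined using logistic regression analyses". The denominator is purchases. The primary hypothesis is one statement about food and drink items together, and the secondary outcomes are likewise described over intended purchases as a whole.

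Under Secondary outcomes the plan adds: "All analyses will be adjusted for key covariates". The covariates are not named. The protocol mentions no random effect, GEE, robust standard error or other allowance for repeated choices, and gives no ICC. It also does not say whether the three categories enter one model or three.

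**The concern.** Ordinary logistic regression assumes that rows are independent. Three choices by one shopper are unlikely to be. The protocol itself classes participants as high or low sugar purchasers from what they usually buy in these categories, sets a quota on that status, and plans to test usual sugar consumption as an effect modifier.

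Because the label does not vary within a person, positive correlation inflates the true variance of the label effect, and a model that ignores it does not see the inflation. Reducing the data to a count of high sugar choices out of three does not help. A standard binomial logistic model for that count has the same likelihood, up to a constant, as three independent rows, and so gives the same standard errors.

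At stake is the 5% significance level named under Sample size calculations. It applies to the label comparisons in Trial 1, from which the two labels for Trial 2 are chosen, and to the Trial 2 comparisons that are meant to inform labelling policy.

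**Working it through.** **Inputs from the protocol.** Three tasks per participant and one label per participant (Trial 1 methods). 144 per group, about 10% unusable surveys, rates of 64% against 28% to 47%, and "with a statistical significance level of 5% and 80% power" (Sample size calculations).

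**Assumptions.** Two-sided testing, since sidedness is not stated. ICC from 0.05 to 0.5, since none is given. Exactly three purchases per person, relaxed below.

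**Step 1: the plan's own figure.** Two proportions, 64% against 47% (the smallest difference quoted), with unpooled variance:

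n = (1.96 + 0.8416)² × (0.64 × 0.36 + 0.47 × 0.53) / 0.17² = 130.2 usable per group.

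130.2 × 1.1 = 143.2, which rounds up to 144. The stated figure is reproduced with one binary outcome per participant, so the sample size does not count three choices as independent information.

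**Step 2: error rate if choices are pooled as independent rows.** The design effect is 1 + (3 − 1) × ICC. The naive standard error is 1/√(design effect) of the correct one. True type I error is 2 × [1 − Φ(1.96/√(design effect))].

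| Assumed ICC | Design effect | Naive SE as share of correct SE | True type I error |
|---|---|---|---|
| 0 | 1.0 | 100% | 5.0% |
| 0.05 | 1.1 | 95% | 6.2% |
| 0.1 | 1.2 | 91% | 7.4% |
| 0.2 | 1.4 | 85% | 9.8% |
| 0.3 | 1.6 | 79% | 12.1% |
| 0.5 | 2.0 | 71% | 16.6% |

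**Step 3: simulation check.** Two arms of 130 usable participants, three correlated choices each, no true effect, 10,000 runs per setting. With a common rate of 64%, the pooled-row Wald test rejected in 7.1%, 9.5%, 12.5% and 15.9% of runs at ICCs of 0.09, 0.19, 0.29 and 0.49. With category rates of 45%, 60% and 75% and no category term, inflation was lower: 6.6% to 13.8% at ICCs of about 0.09 to 0.45. With a person-level (cluster-robust) standard error, rejection was 4.5% to 5.3% in every setting.

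**Step 4: fewer than three purchases.** If everyone made only two, the design effect would be 1 + ICC. At ICC 0.3 that is 1.3, and the error rate is 2 × [1 − Φ(1.96/√1.3)] = 2 × [1 − Φ(1.719)] = 8.6% instead of 12.1%.

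**Step 5: power after allowing for correlation.** Three choices from 144 people give 432 rows per group. Effective size is 432/(1 + 2 × ICC), and 90% of it is usable. Taking 64% against 47% as the pooled rates:

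- ICC 0.3: 432/1.6 = 270, of which 243 usable; power about 97%.
- ICC 0.5: 432/2 = 216, of which 194 usable; power about 92%.
- ICC 1: 432/3 = 144, of which about 130 usable; power about 79%.

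Even the extreme case stays close to the planned 80%.

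**The case against.** The strongest reply is that the protocol never says the rows will be treated as independent. GEE, random-intercept and cluster-robust models are all forms of logistic regression, so the current wording does not exclude them. The plural in the primary outcome text could mean one model per category, which has one row per person and no inflation from this source. The sample size fits that reading too, since it rests on one binary outcome per participant. Variance estimation is often left to a statistical analysis plan, and one may exist that is not shown. The ICC is assumed, and the high/low purchaser classification describes usual shopping, not the correlation among the experimental choices.

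Much of this stands. A reader might infer that the plan commits to independent rows, or that the 5% level is definitely lost. The text supports neither. A reader might also infer that the model omits food category. That is not established either, because the key covariates are unnamed. Nor is a combined food-and-drink estimate an error: it is what the primary hypothesis asks for. The Background does note that "However, there is limited evidence of labelling effects on actual or intended food purchases for foods other than sugar-sweetened beverages", which makes results by category useful. But the suggestion that a beverage effect would be reported as a food effect is speculation about reporting.

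What does not fall away is that the protocol names a method and an outcome over purchases, and its own design breaks that method's independence assumption if the method is applied in its ordinary form to pooled choices. Adjusting for covariates may reduce within-person correlation but cannot be relied on to remove it. If separate models were intended, the single primary hypothesis would become three tests with no stated rule for combining them, so the wording needs attention on either reading.

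**Conclusion.** The point holds conditionally. If the three categories are pooled, as the single hypothesis suggests, and no allowance is made for the participant, the nominal two-sided 5% test has a true error rate of about 6% to 17% for an assumed ICC of 0.05 to 0.5 and three purchases per person. Smaller numbers of purchases, or differing category rates without a category term, bring this down somewhat. At an ICC of 0, or with each category modelled separately, this source adds nothing.

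The same reasoning applies to the pooled secondary outcomes and, through the shared analysis section, to Trial 2. The Trial 2 methods do not restate the number of tasks, so the figures carry over only if there are again three. This is a specification to settle before analysis; it does not undermine the design or the sample size.

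**What to change.** Under Primary outcome, state that the pooled analysis is a task-level logistic model with food category as a fixed effect and the participant as the cluster, by GEE, by cluster-robust standard errors or by a participant random intercept. Name one of these, because a random intercept gives a participant-specific odds ratio and the other two a population-averaged one. Under Secondary outcomes, apply the same participant-level handling to the pooled linear and logistic models. Say how choosing no product enters the denominator. Category-specific label effects can be reported as supportive results. If one model per category was intended instead, say so and state how the three results bear on the single primary hypothesis.

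The cost is a few sentences of analysis text and intervals wider than the naive ones. The sample size of 144 per group need not change.
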